### Study participants

The participants in the pre- and post-intervention surveys will be sexually active women with disabilities in their reproductive age (i.e. 15–49 years). Specifically, women with moderate to severe physical disability (including albinism and leprosy) and visual impairments will be included. We focused on physical and visual impairments partly because they are the dominant disabilities in Ghana [27]. We exclude hearing/speech impairments and mental disabilities partly because deaf and mentally-ill women/girls have needs that are unique and often require further targeting and specialized services (e.g. sign language) that maybe impossible to implement within the time allowed for this project.

### Sample size estimation

To estimate a minimum sample size that will allow for small effect sizes to be detected, we used the sample size estimation formula below:$$n=Deff\times \frac{{\left\{Z_{1-\beta }\sqrt{ [p_{1}(1-p_{1} )+p_{2}(1-p_{2}) ]}+{Z}_{1-\alpha/2}\sqrt{\left[2\overline{p }(1-\overline{p })\right]}\right\}}^{2}}{(1-NR)\times {(p_{1}-p_{2})}^{2}} {Z}_{1-\alpha / 2}$$
where $${\overline{p}}={\frac{{p_1}+{p_2}}{2}}$$; $${p}_{1}=13.1\%,$$ which is the anticipated population proportion of modern contraceptive use at baseline based on a recent community-based cross-sectional study among women with disability in Ethiopia that estimated modern contraceptive use prevalence (a key outcome in the current study) [37]; $${p}_{2}=25.1\mathrm{\%},$$ which is the expected prevalence of modern contraceptive use after the implementation of the intervention; $${Z}_{1-\alpha/2}$$ in the formula is the standard normal variate at 5% level of significance; $$NR=10\%$$ is the anticipated non-response/loss to follow-up rate; Deff = 1.1 to adjust for design effect.

Based on these assumptions, the estimated sample size for each arm is 170. As the design contains four arms, the sample ratio is 1:1:1:1. This means that 170 women with disabilities will be recruited into each arm of the study, totalling 680.

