## Methods

### Context

This research will be implemented in the Northern region of Ghana. As indicated earlier, the region has one of the highest unmet need for sexual and reproductive health services and the lowest supervised delivery rates in the country. For instance, while 25% of married women aged 15–49 years in Ghana used modern contraceptives in 2017, only 16.8% did so in the region [31]. The project would be implemented in four districts with the highest disability rates in the region: Central Gonja (3.6%), West Gonja (3.8%), Savlugu (4.6%), and Bunkprugu-Nankpanduri (5.4%) districts [32]. While the four districts chosen for the experiment are geographically distant enough to limit cross-contamination of participants, the districts are nevertheless socially, culturally and economically similar. This similarity will ensure comparability of results.

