## Discussion

In recognition of the relative marginalization of many persons with disability across the world, the United Nations Convention on the Rights of Persons with Disabilities guarantees persons with disabilities the fundamental human rights to access “the same range, quality and standard of free or affordable healthcare and programs as provided to other persons, including those in the area of sexual and reproductive health and population-based public health programs” [28]. While this recognition may have contributed to heightening global awareness about the marginalization and rights of persons with disabilities, available evidence suggests that persons with disabilities still face numerous challenges in accessing and utilizing essential reproductive health services [3] and this affects their quality of life [3, 5–15]. Impediments to receiving required health services include attitudinal biases of health and social service providers, physical barriers in clinical settings, and poor dissemination of information [5–7]. Lack of access to sexual and reproductive health information and services for women with disability constitutes a form of social exclusion and certainly a violation of their right to appropriate and quality sexual and reproductive health care as provided for in the United Nations Convention on the Rights of Persons with Disabilities [28]. Such exclusion could potentially undermine efforts to achieve equitable or universal healthcare access as envisaged in Sustainable Development Goal 3. It is within this context that the study herein proposed becomes relevant. Through this study, we aim to generate research evidence to support effort to achieve universal access to health. This research is also expected to help identify determinants of sexual and reproductive health services utilization as well as barriers to accessibility of sexual and reproductive health information and services currently being provided by both the public and private health sectors in Ghana. It will generate important evidence to inform local health policies/programmes to increase access to sexual and reproductive health among women with disability and as well strengthen local health system capacity to provide disability-sensitive sexual and reproductive healthcare services. In particular, if the proposed interventions are shown to be effective, same or similar interventions could be deployed in similar settings in Ghana and Africa to bridge the reproductive health inequality gap between women with disabilities and women without disability.

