
The proposed study however has potential limitations. The first is related to recruitment and retention of participants over the 12 months study period. We anticipate challenges in identifying women with disabilities due to stigma associated with disability. To address this challenge, we have proposed the use of community health volunteers who are usual community members to help bridge the gap in identifying women/girls with disabilities in the community. The second limitation is related to the quasi-experimental design of the study. Generally, the evidence from a cluster randomized clinical trial for example is at a much higher level than a quasi-experimental study. However, participants in this study will not be randomly assigned to the interventions as in a randomized control trial. Similarly, participants in the control group will not receive any of the interventions. We note however that participants in the four districts are socially, culturally and economically similar and this similarity will ensure comparability of results. Finally, 12 months may not be sufficiently long enough to expect dramatic positive changes in sexual and reproductive health outcomes of women with disabilities in a context like northern Ghana, where reproductive health outcomes in the general population are already poor.

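### The protocol says its sample size allows small effects to be detected, but its own inputs support only a rise of about 13 percentage points in contraceptive use

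*Protocol article*

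**What the plan says.** The Sample size estimation section states the aim of the calculation: "To estimate a minimum sample size that will allow for small effect sizes to be detected". It then gives a two-proportion formula with these inputs:

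- Baseline modern contraceptive use of 13.1%, taken from a study of women with disability in Ethiopia.
- A second proportion of 25.1%, "which is the expected prevalence of modern contraceptive use after the implementation of the intervention". No basis for this value is given.
- A Z value that "in the formula is the standard normal variate at 5% level of significance", written with 1 − α/2 and therefore two-sided.
- 10%, which "is the anticipated non-response/loss to follow-up rate".
- "Deff = 1.1 to adjust for design effect".

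The power term appears in the formula, but no value is given for it. The stated result is 170 women per arm, 680 in all.

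The Design section says the same women are surveyed before the intervention and at 12 months. The Data processing and analysis section names difference-in-difference as the main method. Among the limitations, the Discussion says that "12 months may not be sufficiently long enough to expect dramatic positive changes in sexual and reproductive health outcomes".

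**The concern.** A reader told that the trial is sized for small effects will take a non-significant contrast as evidence against even a modest benefit. The effect actually used for sizing is a near-doubling within a year, and the protocol itself doubts that dramatic change can be expected in that time. If the realistic gains are smaller than the one planned for, the trial will often fail to show them, and nothing in the sample size section would warn the reader of this.

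**Working it through.** **Inputs.** From Sample size estimation: p1 = 0.131, p2 = 0.251, two-sided α = 0.05 (z = 1.96), loss 10%, design effect 1.1, 170 per arm. Assumed, because the documents give no value: power 80% (z = 0.8416), and a within-woman correlation ρ between the two surveys of 0 to 0.7. Also assumed as a yardstick: Cohen's h = 0.2 as a conventionally small effect. The protocol does not define small.

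**The plan's own figure.** With p̄ = 0.191:

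- 1.96 × √(2 × 0.191 × 0.809) = 1.0896
- 0.8416 × √(0.131 × 0.869 + 0.251 × 0.749) = 0.4624
- (1.0896 + 0.4624)² / 0.12² = 167.3, so 168 per arm before inflation
- 167.3 × 1.1 / 0.9 = 204.4, so 205 per arm after inflation

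The stated 170 lies close to the uninflated figure and is not reproduced once the plan's own loss and design effect are applied at 80% power. How 170 arose is a separate question. What matters here is the sensitivity that 170 per arm gives.

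**Size of the planned effect.** 25.1 − 13.1 = 12.0 points, and 25.1 / 13.1 = 1.92. Cohen's h = 2·arcsin√0.251 − 2·arcsin√0.131 = 1.0495 − 0.7407 = 0.31. An h of 0.2 from 13.1% corresponds to 20.5%, a rise of about 7.4 points.

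**Power on the plan's formula.** Effective n = 170 × 0.9 / 1.1 = 139.1 per arm. For a difference d, power = Φ{[d√n − 1.96√(2p̄(1 − p̄))] / √(p1(1 − p1) + p2(1 − p2))}.

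- 13.1% against 20.5%: (0.877 − 1.037) / 0.526 = −0.30, power about 38%
- 13.1% against 25.1%: (1.415 − 1.090) / 0.549 = 0.59, power about 72%
- 80% power is reached at d = 0.133: (1.571 − 1.104) / 0.555 = 0.84

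If loss and design effect are ignored (n = 170), power is about 45% for the small effect and 81% for 12 points, and the minimum detectable difference is 11.9 points.

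**Under difference-in-difference.** Take both arms at 13.1% at baseline, the control arm unchanged, and n = 139.1 per arm. Then SE² = {2p1(1 − p1)(1 − ρ) + p1(1 − p1) + p2(1 − p2) − 2ρ√[p1(1 − p1)p2(1 − p2)]} / n, and power = Φ(d/SE − 1.96).

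| Assumed ρ | Power, small effect (d ≈ 0.074) | Power, 12 points | Minimum detectable difference at 80% |
|---|---|---|---|
| 0 | 0.0744/0.0602: 23% | 0.12/0.0617: 49% | 17.7 points |
| 0.3 | 0.0744/0.0505: 31% | 0.12/0.0518: 64% | 14.7 points |
| 0.5 | 0.0744/0.0428: 41% | 0.12/0.0440: 78% | 12.4 points |
| 0.7 | 0.0744/0.0333: 61% | 0.12/0.0345: 94% | 9.5 points |

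The lowest value, 9.5 points, takes 13.1% to 22.6%, which is h = 0.25 and still above 0.2. Combining ρ = 0.7 with no loss and no design effect gives 0.0744/0.0301 = 2.47, and 2.47 − 1.96 = 0.51, so power of about 69% for the small effect. That is still short of 80%.

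**The case against.** **Small is undefined.** The protocol sets no threshold, and on the yardstick used here h = 0.31 is nearer to 0.2 (small) than to 0.5 (medium). This stands as a comment on how far the wording is off. It does not rescue the claim, because an effect at the conventional small value has only 38% power on the plan's own formula.

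**The two-proportion figures are not those of the main analysis.** This is correct, and for that reason 13.3 points should not be given alone. The difference-in-difference range is wide and depends on a correlation that the documents do not report. Every value in it is still above a conventionally small effect.

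**The duration is already disclosed.** It is, as a hedged limitation on reproductive health outcomes in general. A reader might infer that the protocol calls 12 months too short for the planned effect. It says only that the period may not be long enough for dramatic change. The limitation also says nothing about what the sample size can detect.

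**Two stronger readings go beyond the documents.**

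- The Context section reports that "only 16.8% did so in the region", and the Discussion hopes such interventions could "bridge the reproductive health inequality gap between women with disabilities and women without disability". One might subtract 13.1% from 16.8% and say the trial would miss complete closure of a 3.7-point regional gap. But 13.1% describes women with disability in Ethiopia, and 16.8% describes married women in Ghana's Northern Region. Participants need not be married. The protocol states no such gap.
- One might infer that a non-significant package would be reported as ineffective and not scaled up. The protocol sets a 0.05 threshold and a 95% confidence level, and says what could follow if the interventions are shown to be effective. It does not say how a null result will be reported.

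**Conclusion.** The statement that the sample size allows small effects to be detected is contradicted by the inputs in the same section. On the plan's formula with its own loss and design effect, power is about 38% for a conventionally small effect and about 72% for the planned 12 points. The minimum detectable difference is about 13.3 points at an assumed 80% power, or 11.9 if loss and design effect are ignored. Under difference-in-difference it is about 17.7 to 9.5 points for an assumed ρ of 0 to 0.7.

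These figures rest on the borrowed 13.1% baseline, on binomial variation with a design effect of 1.1 and no other source of between-district change, and on a control arm that stays flat. The conclusion does not depend on the choice between the readings, since none reaches 80% power for a small effect. The error lies in a stated property of the design. It affects how non-significant results will be read, not how the trial is conducted.

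**What to change.** In Sample size estimation, delete the reference to small effects and state what the trial can detect: about 13 points at 80% power on the plan's formula with 10% loss and a design effect of 1.1. Give alongside it the range under difference-in-difference and the within-woman correlation assumed. A figure of 12 points should not be offered as detectable with 80% power on the plan's formula, since 170 per arm gives about 72% for it.

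In the limitations paragraph of the Discussion, add that a non-significant 12-month result does not exclude gains smaller than this difference. Report each contrast with control as an estimate with its 95% confidence interval. Do not write a 3.7-point regional gap into the text.

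The cost is wording only, with no added participants or follow-up. The stated sensitivity becomes less favourable.

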### Design

A quasi-experimental quantitative study design, involving pre- and post-intervention surveys, will be used to test the effect of three inter-related interventions. Although evidence from designs such as cluster randomized clinical trial is typically at a much higher level than a quasi-experimental study, we chose a quasi-experimental design because the four study districts were purposively selected. Therefore, it was not possible to randomize the districts as clusters.

The inventions are *(1) capacity building in disability-centred sexual and reproductive health and rights information and services delivery for healthcare providers; (2) support for women with disabilities to access disability-unfriendly healthcare infrastructure and (3) one-on-one regular sexual and reproductive health and rights education, information provision, and referral*. While detailed description of each intervention is provided later, it is important to specify that the first two interventions are at the health-facility level while the third one is at the individual/family level.

In this quasi-experimental design, there are four arms; each to be based in one district determined using a simple random sampling procedure. In the first arm, eligible women with disabilities in the Savelugu Municipality will be exposed to all the three interventions. In the second arm, eligible women with disabilities in Bunkprugu-Nankpanduri district will be exposed to only the two-health facility-level interventions. The third arm (in Central Gonja District) will be exposed to only the individual level intervention. The forth arm (based in West Gonja district) will constitute the control group (i.e. women with disabilities will not be exposed to any intervention). To assess the effect of each of the three arms of interventions, we will first conduct a cross-sectional pre-intervention survey among all women with disabilities in each intervention arm. This survey will aim to collect baseline data on several outcomes including awareness about modern contraceptives, use of modern contraceptives, including antenatal care attendance and skilled delivery among those who have given birth before. The same survey will be repeated at the end of the intervention (i.e. 12 months) on the same women in all arms of the experiment.

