### Data processing and analysis

Data from the online REDCap platform will be downloaded and exported as excel files. All data files will then be exported into STATA version 15 for cleaning, coding and possible recoding and analysis. Data cleaning will be done by identifying outliers/anomalies and checking for consistency among and across variables. Frequency distributions and cross tabulations will specifically be run to aid the data cleaning process. Basic descriptive statistical analyses will be performed to describe socio-demographic characteristics of respondents, as well as awareness about, and use of modern family planning/contraceptive methods.

In addition to using descriptive statistics to describe important characteristics and changes in SRH outcomes in each experimental arm, the main statistical analytical method will be Difference-in-Difference Analysis. This analytical technique will allow us to detect the true effect of each intervention in comparison to the control group, while controlling for confounders. The statistical analysis will particularly involve comparison of changes in key outcome variables across all arms of the experiment. In addition, Chi-square tests of association will be performed to understand factors associated with sexual and reproductive health services utilization, including examining association between a number of independent variables (e.g. age, sex, education, and disability type) and dependent variables (e.g. awareness about modern family planning/contraceptives, and use of modern contraceptives). Multiple logistic regression models will then be fitted to examine the relationship between dependent variables (e.g. modern contraceptive use) and independent variables. Furthermore, for continuous variables such as number of antenatal visits, multiple linear regression models will be fitted. Finally, cost-effectiveness analyses will be done on the three-intervention arms vis a vis changes in key outcome measures to identify which of the three interventions is likely to yield greater impact with lower costs. For all the inferential quantitative analysis, confidence level will be set at 95% and p-value of less than 0.05 will be taken as demonstrating statistical significance.

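### The 170 per arm is derived for an independent two-proportion contrast, while the main analysis is a difference-in-differences on the same women, so its adequacy depends on a correlation and a control-arm change that are not stated

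*Protocol article*

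**What the plan says.** All places are in the Methods of the protocol article.

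- **Sample size estimation** uses a two-proportion formula. The first proportion is 13.1%, "which is the anticipated population proportion of modern contraceptive use at baseline". The second is 25.1%, "which is the expected prevalence of modern contraceptive use after the implementation of the intervention". The critical value "is the standard normal variate at 5% level of significance" enters at 1-α/2, so the test is two-sided. NR = 10% "is the anticipated non-response/loss to follow-up rate", and "Deff = 1.1 to adjust for design effect". The power term appears in the formula without a value. The result is 170 per arm, 680 in total.
- **Design** repeats the survey at 12 months "on the same women in all arms of the experiment".
- **Data processing and analysis** says that "the main statistical analytical method will be Difference-in-Difference Analysis", with each intervention compared with control, and that a "p-value of less than 0.05 will be taken as demonstrating statistical significance".

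**The concern.** The formula and the analysis address different contrasts. Taken literally, the two inputs describe an uncontrolled before-after change in one arm, with the two surveys treated as different women. The planned estimator is the change in an intervention arm minus the change in control. It has four proportions, so four variance terms, and two covariances that reduce the variance because each woman is measured twice. The formula contains neither the control change nor the covariances.

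This is not detail left to a later analysis plan. The article prints the formula and takes the recruitment target from it. As it stands, a reader cannot tell what power 170 per arm gives for the result that will be reported. A non-significant DiD could be read as failure of an arm when it may only reflect low precision, and the cost-effectiveness comparison would rest on the same estimates.

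**Working it through.** **Step 1. The plan's own figure.** p1 = 0.131, p2 = 0.251, mean 0.191, difference 0.12, two-sided 5%. Power is not stated; I assume 80%. The printed formula ends with a stray Z, which I treat as a typesetting remnant.

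- p1q1 = 0.131 × 0.869 = 0.1138; p2q2 = 0.251 × 0.749 = 0.1880; 2 × 0.191 × 0.809 = 0.3090.
- Before inflation: n = [0.8416 × √0.3018 + 1.9600 × √0.3090]² / 0.12² = (0.4624 + 1.0896)² / 0.0144 = 167.3.
- With Deff and loss: 167.3 × 1.1 / 0.9 = 204.4, or about 205.

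The stated 170 matches only the uninflated figure. With 170 recruited, the plan's own adjustments leave 170 × 0.9 / 1.1 = 139.1 effective women per arm. The simple contrast then has about 72% power (73% with an unpooled variance).

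**Step 2. The DiD.** Assumptions that are not in the article: control stays at 13.1%, the same r applies in both arms, and the test is a Wald test on the risk-difference scale.

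V(r) = [p1q1 + p2q2 - 2r√(p1q1 p2q2)] + 2 p1q1 (1 - r)

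Power = Φ(0.12 / √(V / 139.1) - 1.96)

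The largest r compatible with 13.1% and 25.1% is √[(0.131 × 0.749) / (0.869 × 0.251)] = 0.67. In the table, recruited n includes Deff and loss.

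| r | V | Power at 170 recruited | Recruited n per arm for 80% | Detectable DiD at 80%, points |
|---|---|---|---|---|
| 0 | 0.5295 | 49% | 353 | 17.3 |
| 0.3 | 0.3734 | 64% | 249 | 14.5 |
| 0.5 | 0.2694 | 78% | 180 | 12.3 |
| 0.6 | 0.2174 | 86% | 145 | 11.1 |
| 0.67 | 0.1809 | 91% | 121 | 10.1 |

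Power reaches 80% at r of about 0.53. V(r) falls below the simple contrast's 0.3018 at r of about 0.44; above that, the DiD is the more precise contrast at the same n.

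**Step 3. Control-arm change.** With the same 139.1 per arm:

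- Control alone rises 3 points (to 16.1%) and the intervention arm stays at 25.1%, so the true DiD is 9 points: power is 30% at r = 0 and 52% at r = 0.5.
- Both arms rise by the same 3 points (16.1% and 28.1%), so the DiD stays at 12: power is 47% at r = 0 and 75% at r = 0.5.

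**Step 4. Separating the two problems.** With 205 recruited, as the formula yields at 80% (167.7 effective), DiD power is 57% at r = 0, 72% at 0.3, 85% at 0.5 and 91% at 0.6, crossing 80% at r of about 0.43. The inflation slip therefore explains part of the deficit. The mismatch explains the dependence on r.

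**The case against.** The strongest defence is that pairing helps. The same woman answering the same question 12 months apart will not give unrelated answers, so r = 0 is a mathematical bound and not a forecast. Above r of about 0.44 the DiD outperforms the simple contrast, and above about 0.53 the 170 gives at least 80%. If control stays flat, the two-proportion formula can also be read as an endline comparison between arms, which is a common planning shortcut. All of this stands. It shows that the size may be adequate under some correlations, but the article states none.

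Three stronger readings are tempting, and the document does not support them:

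- **A reader might infer that power is 49% to 78% on the plan's own inputs.** It is not. The correlation and the flat control are my assumptions, and 78% is not a ceiling: with control flat, the feasible range runs to about 91%.
- **A reader might infer that any background rise in use erodes the tested effect.** A rise common to both districts largely cancels in a DiD. Only a rise confined to control, with 25.1% held fixed, reduces it. The article does not say whether 25.1% includes background trend.
- **A reader might attribute the whole shortfall to the DiD.** Step 4 shows that part comes from the missing inflation.

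The scale is also not stated. A logit-scale DiD would have less power (about 39% at r = 0 and 65% at r = 0.5 with 139 effective women), and the planned adjustment for confounders is not reflected in any of these figures.

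**Conclusion.** The point holds as a mismatch: the printed calculation does not describe the planned main analysis, and the two quantities that determine its power are not given. At 170 recruited per arm, with control flat and a risk-difference Wald test, power for a 12-point DiD runs from about 49% to 91% across the feasible correlations. The document does not establish that the trial is underpowered; it establishes that the adequacy of 170 rests on an unstated r above about 0.53 and on what happens in control. I am confident of the mismatch and of the arithmetic, and only moderately confident of where in the range the true power lies. The 170-versus-205 discrepancy is a separate error that should be reported as such; it depends on the assumed 80% power, although higher power would only widen the gap.

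**What to change.** Keep 170 per arm and change the justification:

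- Replace the two-proportion formula with the paired-binary DiD variance V(r) above, divided by the effective number per arm. For a control arm that moves from pc0 to pc1, replace the last term by pc0qc0 + pc1qc1 - 2r√(pc0qc0 pc1qc1).
- State the target power, the assumed within-woman correlation and its source, the assumed control-arm change, and whether 25.1% includes background trend.
- Report power, or the detectable DiD, for 170 recruited per arm over r = 0 to about 0.67, naming the scale of the DiD model.
- Correct the inflation step, or say openly that 170 is the figure before design effect and loss.

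The cost is a recalculation and a rewritten paragraph, with no extra participants. The downside is that the claim that 170 is enough becomes conditional and, over most of the range, less favourable.

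### The 170 women per arm cannot be obtained from the printed sample size formula at any conventional power: power is not stated, and 170 corresponds to about 72%

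*Protocol article*

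**What the plan says.** The section on sample size estimation in the protocol article introduces its calculation with "we used the sample size estimation formula below". The formula is the usual comparison of two proportions, multiplied by a design effect and divided by one minus the non-response rate. As printed, it also carries an extra Z(1−α/2) after the fraction.

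The inputs given are:

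- p1 = 13.1%, anticipated modern contraceptive use at baseline.
- p2 = 25.1%, "which is the expected prevalence of modern contraceptive use after the implementation of the intervention".
- Z(1−α/2), which "in the formula is the standard normal variate at 5% level of significance".
- NR = 10%, which "is the anticipated non-response/loss to follow-up rate".
- Deff = 1.1.

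Z(1−β) stands in the formula but receives no value, and no power is stated anywhere in the article. The section then concludes "Based on these assumptions, the estimated sample size for each arm is 170", for a total of 680 over four arms. Its stated purpose is "To estimate a minimum sample size that will allow for small effect sizes to be detected".

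The section on data processing and analysis names Difference-in-Difference as the main method and says that a "p-value of less than 0.05 will be taken as demonstrating statistical significance".

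**The concern.** The article gives a formula, all inputs but one, and an answer that is said to follow from them. A reader can therefore solve for the missing input and see whether the answer is plausible. It is not: no customary power returns 170.

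The 170 per arm and 680 in total are repeated in the abstract and in the sampling procedure, and this is the only justification offered for them. A reader will assume that 680 already allows for the design effect and for 10% loss at a customary power. The printed formula does not bear that out. The printed formula also has a stray term, so nobody can check the number without first deciding what the formula is meant to be.

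**Working it through.** **Inputs.** All come from the sample size section: p1 = 0.131, p2 = 0.251, difference d = 0.120, mean p̄ = (0.131 + 0.251)/2 = 0.191, Z(1−α/2) = 1.960, Deff = 1.1, NR = 0.10. Power is not stated, so 80%, 85% and 90% are assumptions that cover the customary range.

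**Formula, without the trailing Z(1−α/2).**

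n = (Deff/(1 − NR)) × {Z(1−β)·A + Z(1−α/2)·B}² / d²

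- A = √(0.131×0.869 + 0.251×0.749) = √0.3018 = 0.5494
- B = √(2×0.191×0.809) = √0.3090 = 0.5559
- Deff/(1 − NR) = 1.1/0.9 = 1.222

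**Attempt to reproduce 170 at 80% power.** Z(1−β) = 0.8416.

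- Unadjusted: (0.8416×0.5494 + 1.960×0.5559)² / 0.0144 = (0.4624 + 1.0896)² / 0.0144 = 167.3, rounded up to 168.
- With Deff: 167.3 × 1.1 = 184.0.
- With Deff and NR: 184.0 / 0.9 = 204.4, rounded up to **205** per arm (820 in total).

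The stated figure is not reproduced. At other power levels:

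| Power | Unadjusted n | With Deff and NR |
|---|---|---|
| 70% | 131.8 | 161.1 |
| 75% | 148.0 | 181.0 |
| 80% | 167.3 | 204.4 (205) |
| 85% | 191.1 | 233.6 (234) |
| 90% | 223.4 | 273.1 (274) |

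**Working back from 170.** The effective number per arm is 170 × 0.9/1.1 = 139.1.

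- Z(1−β) = (√(139.1 × 0.0144) − 1.0896)/0.5494 = (1.4152 − 1.0896)/0.5494 = 0.593, so power is **72.3%**.
- Holding p1 at 13.1%, the same 139.1 gives 80% power for p2 of about 26.4%, a difference of about 13.3 points.

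**Trailing Z(1−α/2) taken literally as a factor.** At 80% power, 204.4 × 1.960 = 400.7, about 401 per arm. With 170 per arm, Z(1−β) = (√(139.1 × 0.0144/1.960) − 1.0896)/0.5494 = −0.143, so power is about 44%. The stated 170 does not follow on this reading either.

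**Other forms at 80% power, with both inflations.** One-sided 5% gives 160.9, unpooled variance 201.1, arcsine 201.2 and continuity correction 224.9. None is within 3% of 170.

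**What does come close to 170.**

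- The unadjusted 80% result of 168, with Deff and NR both left out. At 170 women, all analysed, power is 80.6%.
- One-sided 5% and 85% power with only one inflation: 168.2 with Deff alone, 169.9 with NR alone.

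Both routes contradict the printed formula.

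**How far these figures carry to the main analysis.** The formula compares two independent proportions. The main analysis compares changes in the same women with changes in the control arm, and its variance depends on the within-woman correlation ρ, which the article does not give. As an illustration, assume that control stays at 13.1%, the effective n is 139.1 per arm, and the Difference-in-Difference is linear:

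Var = {p1q1 + p2q2 − 2ρ√(p1q1·p2q2) + 2·p1q1(1 − ρ)}/139.1, with p1q1 = 0.1138 and p2q2 = 0.1880.

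- ρ = 0: variance 0.5295/139.1, standard error 0.0617, power about 49%.
- ρ = 0.25: about 61%.
- ρ = 0.5: standard error 0.0440, power about 78%.
- ρ = 0.7: about 94%.

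The 72% lies inside this range but is not the power of that analysis.

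**The case against.** The strongest reply is that the article claims no power. With Z(1−β) left open, 170 does solve the formula at about 72%, so 80% is a standard brought in from outside. That stands as far as it goes: 205 rests on an assumed 80%, and the article makes no 80% claim that could be called false. But the article says that the answer rests on stated assumptions when one of them is missing, and the only value that closes the gap is one that few planners would choose without saying so.

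A second reply is that a journal article leaves details to the full protocol. That would excuse an omission. It does not excuse a formula, inputs and answer that are all printed and cannot be reconciled at a customary power.

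A third reply is that dropping the trailing Z(1−α/2) alters the printed formula. It does, so both readings are shown; 170 fails under each.

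Three stronger readings are tempting, and the article does not support them:

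- *That Deff and NR were certainly left out.* The unadjusted result is 168, not 170, and a second route also lands near 170. The cause is conjecture.
- *That the trial itself has 72% power.* That figure belongs to the printed comparison. The power of the Difference-in-Difference analysis may be lower or higher, depending on a correlation that is not given.
- *That the sample size section contradicts the Discussion.* The Discussion says that "12 months may not be sufficiently long enough to expect dramatic positive changes in sexual and reproductive health outcomes". This is a hedged, disclosed limitation with no number attached, and it does not conflict with p2 = 25.1%. Calling a 12-point difference small is loose wording (Cohen's h is 0.31, between the conventional 0.2 for small and 0.5 for medium), not an arithmetic error.

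**Conclusion.** The point holds in a limited form. Z(1−β) has no stated value, the printed formula contains a stray term, and 170 per arm is not reproduced at 80%, 85% or 90% power. With the stray term removed, the formula gives 205, 234 and 274 per arm respectively, and 170 corresponds to about 72% power for 13.1% versus 25.1%. At an assumed 80%, the stated size is 35 per arm (205 − 170) below the formula's answer.

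This rests on the stated p1, p2, two-sided 5%, Deff 1.1 and NR 10%, and on reading the trailing Z(1−α/2) as a typesetting slip. It does not show that 680 women are too few for the main analysis, and it does not require more to be recruited. It shows that the justification printed for 680 cannot be relied on as it stands. The description of the effect as small is a minor matter of wording.

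**What to change.** Correct the text of the sample size section and keep 680 women:

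1. State the value of Z(1−β) and the power that it represents.
2. Remove the Z(1−α/2) printed after the fraction.
3. State that, after a design effect of 1.1 and 10% loss, 170 per arm gives about 72% power for 13.1% versus 25.1%, or 80% power for 13.1% versus about 26.4%.
4. Label these figures as the power of the printed comparison of two proportions. Say that the power of the Difference-in-Difference analysis also depends on the within-woman correlation, which is not given.
5. Minor: drop the description of the detectable effect as small, and name the 12-point difference instead.

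If the sponsor prefers to claim 80% power for 25.1% under this formula, the matching figure is 205 per arm (820 in total), not 170.

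The cost is a few sentences and a less favourable stated power. The design, the recruitment target and the analysis do not change.
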